### Incarcerated Participants

The National Institutes of Health has policies that require additional safeguards for certain vulnerable populations. These safeguards are particularly important for incarcerated populations as they may not be able to make a truly voluntary and uncoerced decision regarding their participation in research. CREW is also limited in its ability to contact clients for follow-up services or to compensate clients for time while incarcerated. Regulations for prisoners further include requirements for a prisoner representative on the IRB and certification by the study by the HHS Secretary.

As a result of these regulations, clients that become incarcerated after enrollment in the study will automatically be deemed lost to follow-up. CHWs should check public records at least once a quarter to determine changes in sentencing, release, and/or parole.

# STUDY ASSESSMENTS

## Study Assessments

Medical data, including HIV viral load, from the 300 participants will be obtained from the electronic medical records. The study team will maintain a separate, secure database at UM having information on participant age, race, ethnicity, ZIP code, and group assignment. Additional data on several areas related to HIV management, including medication adherence and self-efficacy will also be collected. Data will periodically be transferred from UM’s secure database to REDCap, UM’s web-based clinical research management application for clinical and translational research. Below lists the assessments that will be used for patient tracking, as well as the CHW training evaluation.

| **Specific Aim 1: Primary Measures** | | Durable HIV viral suppression prevents forward transmission of HIV, making HIV treatment synonymous with HIV prevention. The primary outcome is binary: HIV viral suppression (plasma HIV VL of < 200 copies/mL) at the 12-month follow-up. As part of usual medical care, patients have VL checked every 3 months. Thus, data on the primary outcome will be abstracted from the electronic medical record by a study coordinator. All patients who are not up to date on VL measurements will be encouraged to go to their assigned laboratory (JHS, Quest or LabCorp) to have the test done. By Month-11 of enrollment, the staff will call participants to ensure Exit is scheduled on time. |
| --- | --- | --- |
| Viral Load Suppression | Plasma HIV RNA  (>200 copies / mL) |  |
| **Specific Aim 1: Secondary Measures** | |  |
| ART Adherence | Medication adherence (ACTG Adherence Questionnaire) |  |
| Non-HIV Medical Care | Medical Records |  |
| Hospitalizations | Medical Records |  |

| **Specific Aim 2: Primary Measures** | |
| --- | --- |
| ***Structural*** | |
| Social Determinants of Health | Health-Related Social Needs (HRSN) |
| Racism | Index of Race-Related Stress-Brief (IRRS-B) |
| Food Security | Household Food Insecurity Access Scale (HFIAS) |
| ***Institutional*** | |
| Dr-Pt Interaction | Doctor-patient communication questionnaire: empathy, decision-making, listening |
| HIV Stigma – Clinic Setting | Perceived Discrimination Scale: Discrimination, mistreatment, quality of care, & mistrust from healthcare system |
| ***Community*** | |
| HIV Stigma – Community Setting | HIV Stigma Scale – Short Version: Perceptions of stigma, disclosure concerns, concerns with public attitudes and negative self-image |
| ***Interpersonal*** | |
| Social Support | Frequency of & satisfaction with social support |
| ***Individual*** | |
| Health Outcomes | Medical Outcomes Study HIV Health Survey (MOS-HIV): Quality of life measure for PLH |
| Self-Efficacy | HIV Adherence Self-Efficacy Scale (HIV-ASES): social & psychological determinants of adherence |
| Empowerment | Health Empowerment Inventory: Patient-controlled engagement and involvement in healthcare |
| **Specific Aim 2: Secondary Measures** | |
| Motivational Interviewing | CHWs’ MI training and retention will be measured with the Motivational Interviewing Treatment  Integrity Code (MITI 4), administered by a trained MI expert |
| CHW Delivery Strategies | Participant preferences will be extracted from CHW tracking logs to perform a frequency analysis of delivery preferences. Communication (phone, text, in-person); Setting (clinic, community, home); and Support (education, navigation, social support linkage) |

## Adverse Events and Serious Adverse Event

### Definition of Adverse Events (AE)

Adverse event means any untoward medical occurrence associated with the use of an intervention in humans, whether or not considered intervention-related (21 CFR 312.32 (a)).

### Definition of Serious Adverse Events (SAE)

An adverse event (AE) is considered “serious” if, in the view of either the investigator or sponsor, it results in any of the following outcomes:

- Death
- A life-threatening adverse event (of note, the term “life-threatening” refers to an event in which the subject was at risk of death at the time of the event, rather than to an event which hypothetically might have caused death if it were more severe)
- inpatient hospitalization or prolongation of existing hospitalization
- a persistent or significant incapacity or substantial disruption of the ability to conduct normal life functions
- or a congenital anomaly/birth defect.

Important medical events that may not result in death, be life-threatening, or require hospitalization may be considered serious when, based upon appropriate medical judgment, they may jeopardize the subject and may require medical or surgical intervention to prevent one of the outcomes listed in this definition. Examples of such medical events include allergic bronchospasm requiring intensive treatment in an emergency room or at home, blood dyscrasias or convulsions that do not result in inpatient hospitalization, or the development of drug dependency or drug abuse.

### Classification of an Adverse Event

#### Severity of Event

For adverse events (AEs), the following guidelines will be used to describe severity:

- **Mild** – Events require minimal or no treatment and do not interfere with the subject’s daily activities.
- **Moderate** – Events result in a low level of inconvenience or concern with the therapeutic measures. Moderate events may cause some interference with functioning.
- **Severe** – Events interrupt a subject’s usual daily activity and may require systemic drug therapy or other treatment. Severe events are usually potentially life-threatening or incapacitating. Of note, the term “severe” does not necessarily equate to “serious.”

#### Relationship to Study INTERVENTION

All adverse events (AEs) must have their relationship to study intervention assessed by the clinician who examines and evaluates the subject based on temporal relationship and his/her clinical judgment. The degree of certainty about causality will be graded using the categories below. In a clinical trial, the study product must always be suspect.

- **Related** – The AE is known to occur with the study intervention, there is a reasonable possibility that the study intervention caused the AE, or there is a temporal relationship between the study intervention and event. Reasonable possibility means that there is evidence to suggest a causal relationship between the study intervention and the AE.
- **Not Related** – There is not a reasonable possibility that the administration of the study intervention caused the event, there is no temporal relationship between the study intervention and event onset, or an alternate etiology has been established.

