### Known Potential Benefits

Participants may receive direct benefits from participating in this study. They will receive 12-months of CHW support to engage in HIV care and treatment adherence. CHWs will work with the case managers, accompany patients to appointments, and attend clinical meetings, when possible, to provide updates on patients. In this setting, CHWs will help inform the healthcare team of areas of concern and help the team create more focused and effective individualized interventions enlightened by information CHWs have learned from non-clinical visits with participants as part of their own community-informed approaches to health promotion.

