***Important HIV Management components include:***

- - - - CHW counseling/coaching
      - Medical service support/patient navigator activities: help patients with appointment scheduling/reminders, navigating health system bureaucracy, identifying strategies to maximize their time with the providers
      - Goal setting for VL
      - Individual lifestyle interventions: using MI strategies based on Stages of Change model of behavior counseling
      - Referral to existing community-based resources that may be socially or medically based: tenant advocacy, immigration legal services, domestic violence programs, mental health programs, smoking or substance abuse, etc.

*Note: If agreeable, patient, family and caregiver involvement in these sessions will be highly encouraged. The ultimate goal of these activities is for participants to develop and/or improve self-efficacy and social support to manage their HIV health beyond intervention participation.

- **Months 7-12**

***Maintenance:*** *After the first six months, participants will enter the Maintenance Phase.*

- 1. Contact participants 2-3x per month for check-ins on client status (medication adherence, social needs, etc.); in-person interactions on an as needed basis. Contacts include appointment reminders, facilitating contact with providers, and rescheduling appointments as needed.
  2. Check for rebounding sixty (60) to 90 days before study exit & facilitate access to additional social services and HIV support groups as needed.
     - ***Note***: *Some participants may require intensive face-to-face support in Month-9. Participants at this stage are at risk for “****rebounding****,” where their viral load begins to increase again. Additional attention may be needed to maintain progress.*
     - Discuss these cases with the Pl and Co-I ([name]) who will approve any changes, such as modifying service intensity or altering the type of support delivered (i.e., review ART adherence strategies, as well as the process of maintaining health insurance and social service benefits, including food stamps, housing assistance, transportation vouchers, and mental health support)
     - E.g., The Adult Clinical Immunology Education Initiative provides psychological guidance to PLH.
  3. As the 12-month study period nears conclusion, ensure participants are linked participants to community- and clinic-based social support resources.

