#### Expectedness

The Principal Investigator will be responsible for determining whether an adverse event (AE) is expected or unexpected. An AE will be considered unexpected if the nature, severity, or frequency of the event is not consistent with the risk information previously described for the study intervention.

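### The definitions of Related and Not Related overlap with no rule on which prevails, and SAE reports ask a different causality question

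*Protocol*

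**What the plan says.** Relationship to Study INTERVENTION has every adverse event "assessed by the clinician who examines and evaluates the subject based on temporal relationship and his/her clinical judgment", and adds the caution "In a clinical trial, the study product must always be suspect". It then gives two categories.

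- *Related* holds if the event is known to occur with the intervention, if there is a reasonable possibility that the intervention caused it, "or there is a temporal relationship between the study intervention and event". A following sentence explains that reasonable possibility means evidence pointing to causation.
- *Not Related* holds if there is no reasonable possibility of causation, if "there is no temporal relationship between the study intervention and event onset, or an alternate etiology has been established".

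Each list is joined by *or*. The term temporal relationship is not defined, and no sentence says what to do when an event meets both lists.

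Adverse and Serious Adverse Event Reporting has the Principal Investigator report every SAE to the sponsor whether or not it is considered related. The report must assess whether causation by the intervention is a reasonable possibility. It asks nothing about timing alone.

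On exposure, Known Potential Benefits says of participants: "They will receive 12-months of CHW support to engage in HIV care and treatment adherence". The CHW Intervention section plans about one face-to-face visit a week in the first month, and for months 7 to 12 it says: "Contact participants 2-3x per month for check-ins on client status". Usual care receives no CHW support.

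**The concern.** Two categories meant to split events into related and unrelated should not both be true of the same event. Here they can be. Two clinicians can grade the same event in opposite ways, each following the text.

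Timing is also a weak criterion in this design. CHW support is spread over the whole year, so on an ordinary reading most events in that arm begin while the intervention is under way. A ground that most events in the arm could meet does little to separate those caused by counseling, contact or disclosure from background illness. The intervention is delivered in one arm only, so inconsistent use of the timing ground could affect the arms differently. That is a risk to guard against, not a demonstrated result.

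The second problem is that the grade on the case report form and the causality statement in the SAE report rest on different tests. The same SAE can be *Related* in one and have no reasonable possibility of causation in the other, although nobody has made an error. The reporting section also lets the handling of SAEs that are study endpoints turn on evidence of causation. Hospitalization is both an SAE criterion and an Aim 1 secondary measure, so the causal judgment should be made the same way throughout.

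**Working it through.** The plan states no figure on this point, so there is none to reproduce. The check is whether the two definitions, read as written, can both be true.

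**Inputs**, all from Relationship to Study INTERVENTION:

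- K: the event is known to occur with the intervention
- R: there is a reasonable possibility of causation
- T: there is a temporal relationship
- A: an alternate etiology has been established

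**Rules as written**

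- *Related* = K or R or T
- *Not Related* = (not R) or (not T) or A

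Four yes/no facts give 2 × 2 × 2 × 2 = 16 combinations.

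**T present (8 combinations).** *Related* is always met, whatever K is. *Not Related* depends on R and A, so each row below covers two combinations (K yes, K no).

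| R | A | Related | Not Related | Combinations |
| --- | --- | --- | --- | --- |
| yes | no | met | not met | 2 |
| yes | yes | met | met | 2 |
| no | no | met | met | 2 |
| no | yes | met | met | 2 |

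So 6 of the 8 meet both definitions. Only a reasonable possibility with no alternate etiology is clearly *Related*.

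**T absent (8 combinations).** *Not Related* is always met. *Related* is also met if K or R holds, which is 6 combinations. The other 2 are *Not Related* only.

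**Totals**

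- both definitions: 6 + 6 = 12
- *Related* only: 2
- *Not Related* only: 2
- neither: 0
- check: 12 + 2 + 2 + 0 = 16

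These count logical cases. Some will be rare in practice, and the totals say nothing about how often real events fall in each.

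**Example.** An injury with a known cause in month 5 of CHW support, read as temporally related, has T yes, A yes, R no. It is *Related* through timing and *Not Related* through two grounds. If it is an SAE, the report to the sponsor would say there is no reasonable possibility of causation, while the form may say *Related*.

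**How far timing discriminates.** Suppose T is read narrowly, as onset soon after a contact. At 2 to 3 contacts a month, evenly spaced over a 30-day month, the gap between contacts is 30/3 = 10 to 30/2 = 15 days. Every event in months 7 to 12 would then begin within 10 to 15 days of the previous contact. Whether that counts as a temporal relationship is not stated.

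**After the change proposed below.** *Related* = R and *Not Related* = not R. Of the 16 combinations, 8 are *Related*, 8 are *Not Related*, and none is both.

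**The case against.** The strongest defense is that the grading is not mechanical. The lead-in calls for clinical judgment as well as timing, and the section on time period and frequency of event assessment restricts the judgment to people qualified to diagnose. Consequences are limited: that same section has all AEs documented regardless of relationship and with a description, so a distress or disclosure event remains identifiable. SAEs go to the sponsor whatever the grade. No stopping rule or between-arm comparison is said to use relatedness. A generous timing criterion can also be defended as caution.

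Most of this stands, and it is why the point is small. It does not remove the contradiction. Judgment can decide whether R, T or A holds, but the text does not say which category applies when the answers point both ways. The caution that the product is always suspect leans toward *Related* without saying that it overrides an established other cause.

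A reader might go further and infer that nearly every CHW-arm event would be graded *Related* and none in usual care, so that the monitoring committee would see a false signal of harm. The documents do not support this. The overlap leaves the grade open; it does not force *Related*. Temporal relationship is undefined, so equating it with any onset in the 12 months is only one reading. How relatedness is graded in usual care is not stated, and few intervention-related events would be expected in any control arm that does not receive the intervention. No passage describes a split of relatedness by arm going to the committee or the IRB.

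A reader might likewise infer from Expectedness, where an event is unexpected if "not consistent with the risk information previously described for the study intervention", that an ordinary hospitalization in the CHW arm becomes serious, related and unexpected. The *related* part of that chain is exactly what the text leaves undetermined.

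**Conclusion.** Wrong as written, and minor. Timing alone satisfies *Related*, while no reasonable possibility or an established alternate etiology satisfies *Not Related*. The two categories are therefore not mutually exclusive, and no rule of precedence is given. The SAE report uses a narrower test than the grading rule, so the two can disagree about one event.

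The conclusion rests on reading each list's *or* in its ordinary sense. The likely effect is inconsistent grading of relatedness. Its frequency cannot be estimated, because the Protocol gives no event rates. A difference between arms in how events are graded is possible because contact with the intervention is sustained in one arm only, but it is not shown. The primary endpoint, the randomization and its analysis are unaffected.

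**What to change.** Use one causality test in both Relationship to Study INTERVENTION and Adverse and Serious Adverse Event Reporting. Suggested content:

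- *Related*: there is a reasonable possibility, meaning evidence that suggests causation, that the study intervention caused the event. Timing, prior knowledge that such events occur with the intervention, and any other established cause are weighed in that judgment. Timing is supporting evidence and does not decide the grade alone.
- *Not Related*: every event that does not meet that definition.

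State that the SAE report uses the same assessment, and match the options on the AE form.

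The cost is a few sentences in a protocol amendment with IRB approval, plus the form change. No new staff or procedures are needed. If events have already been graded under the present wording, they should be regraded so that the trial has one standard. The downside is that some events linked by timing alone would no longer be graded *Related*. They would still be recorded, and SAEs would still be reported.

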#### Expectedness

The Principal Investigator will be responsible for determining whether an adverse event (AE) is expected or unexpected. An AE will be considered unexpected if the nature, severity, or frequency of the event is not consistent with the risk information previously described for the study intervention.

### Time Period and Frequency for Event Assessment and Follow-Up

The occurrence of an adverse event (AE) or serious adverse event (SAE) may come to the attention of study personnel during study visits and interviews of a study subject presenting for medical care, or upon review by a study monitor.

All AEs including local and systemic reactions not meeting the criteria for SAEs will be captured on the appropriate case report form (CRF). Information to be collected includes event description, time of onset, clinician’s assessment of severity, relationship to study product (assessed only by those with the training and authority to make a diagnosis), and time of resolution/stabilization of the event. All AEs occurring while on study must be documented appropriately regardless of relationship. All AEs will be followed to adequate resolution.

Any medical condition that is present at the time that the subject is screened will be considered as baseline and not reported as an AE. However, if the study subject’s condition deteriorates at any time during the study, it will be recorded as an AE.

Changes in the severity of an AE will be documented to allow an assessment of the duration of the event at each level of severity to be performed. AEs characterized as intermittent require documentation of onset and duration of each episode.

The Study Coordinator will record all reportable events with start dates occurring any time after informed consent is obtained until 7 (for non-serious AEs) or 30 days (for SAEs) after the last day of study participation. At each study visit, the Study Coordinator will inquire about the occurrence of AE/SAEs since the last visit. Events will be followed for outcome information until resolution or stabilization.

### Adverse and Serious Adverse Event Reporting

All serious adverse events must be reported to the IRB according to regulatory requirements. The Principal Investigator will immediately report to the sponsor any serious adverse event, whether or not considered study intervention related, including those listed in the protocol or package insert and must include an assessment of whether there is a reasonable possibility that the study intervention caused the event. Study endpoints that are serious adverse events (e.g., all-cause mortality) must be reported in accordance with the protocol unless there is evidence suggesting a causal relationship between the study intervention and the event (e.g., death from anaphylaxis). In that case, the investigator must immediately report the event to the sponsor.

All serious adverse events (SAEs) will be followed until satisfactory resolution or until the Principal Investigator deems the event to be chronic or the subject is stable. Other supporting documentation of the event may be requested and should be provided as soon as possible.

# STATISTICAL CONSIDERATIONS

## Statistical Hypotheses

**Primary Efficacy Endpoint(s):**

SPECIFIC AIM 1: Compare the effect of a clinic-based CHW-led MI intervention versus usual care (UC) on HIV health outcomes among Black PLH (n = 300) with uncontrolled viral load (>200 copies/ml). Aligned with the NIMHD Minority Framework for Health and Health Disparities Research, this pragmatic two-arm parallel RCT CHWs will support a multilevel approach to improving HIV care outcomes among Black PLH in Miami-Dade. The primary outcome is HIV viral load suppression at 12-months.

